**Self-rating**					
Demographic information (age, sex, migration background, mother tongue, German language proficiency, education)*			×		
Acculturation (SMAS)			×		
Usefulness of information material (USE)			×	×	×
Knowledge of the disease*			×	×	×
Perceived cultural sensitivity*			×		
Behaviour change*				×	×
Illness perception (Brief-IPQ)			×	×	×
Symptom self-rating (PHQ-9, Core set)			×	×	×
Acceptance of the disease or treatment*			×	×	×
Adherence (MOS)				×	×
Satisfaction with physician (ZAPA)			×	×	×
Health care utilization*				×	×
Quality of life (WHO-5)			×	×	×

-T_1_, within the consultation; T_0_, after informed consent has been given; T_1_, after consultation; T_2_, 8 weeks; T_3_, 6 months; Brief-IPQ, Brief Illness Perception Questionnaire; MOS, Medical Outcomes Study (general adherence); PHQ-9, 9-item version of the Patient Health Questionnaire; SMAS, Stephenson Multigroup Acculturation Scale; USE, Usefulness Scale for Patient Information Material; WHO-5, WHO 5 Well-being Index; ZAPA, questionnaire assessing satisfaction with outpatient care, with a focus on patient participation; *, self-constructed items.

Patients in the intervention group will receive a culturally sensitive version and patients in the control group will receive a standard translated version of brochures. Patients will read the brochures after the end of the consultation, and will be asked to fill in the questionnaire and return it by post using a prepaid envelope (T_1_, after consultation). If patients do not respond, they will be reminded by phone (if possible) after 2 weeks and by post after 3 weeks. At 8 weeks (T_2_) and 6 months (T_3_) after the consultation, patients will be contacted by post and asked to fill in follow-up questionnaires. To ensure a sufficient response rate at each time point, patients will receive an unconditional reimbursement of €5.00, as this measure has been shown to be associated with an increased response rate [18].

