### Secondary outcomes

Perceived usefulness (USE) will additionally be assessed at T_2_ and T_3_, to investigate the perception of usefulness of the information material over time. Differences in the subscales will additionally be assessed. We will additionally assess the effects of the culturally sensitive material on knowledge of the disease (self-constructed items; at T_1_, T_2_, T_3_) and whether adapted patient information material is perceived as more culturally adequate (perceived cultural sensitivity; self-constructed items; T_1_). In addition, the level of implementation of behaviour promoted in the patient information material (behaviour change; self-constructed items; T_2_, T_3_), perception of disease (Brief Illness Perception Questionnaire, Brief-IPQ; T_1_, T_2_, T_3_[19]), symptoms of depression or back pain (Patient Health Questionnaire, PHQ-9, Core set; T_1_, T_2_, T_3_[20,21]), and acceptance of disease and the treatment (self-constructed items; T_1_, T_2_, T_3_) will be investigated. Finally, the effects of the culturally sensitive material on adherence (MOS general adherence items; T_2_, T_3_[22]), Satisfaction with the physician (ZAPA; T_1_, T_2_, T_3_[23]), healthcare utilization (self-constructed items; T_2_, T_3_) and quality of life (WHO 5 Well-being Index, WHO-5; T_1_, T_2_, T_3_[24]) will be assessed.

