### Statistical analyses

The primary outcome (usefulness of written patient information material; USE) will be analyzed by a blinded statistician with a one-sided *t* test comparing the scores on the USE scale between the intervention and the control group. Secondary interval-scaled outcomes will be tested using *t* tests and analysis of covariance (ANCOVA, if baseline measurement of the outcome is available). In additional analyses, we will include acculturation (SMAS) as covariate and conduct subgroup analyses regarding disease, migration background, symptom severity and acculturation. The primary analysis will be performed according to the intention-to-treat principle, including all randomized participants. Missing data will be handled by applying linear mixed models and expectation-maximisation imputation. Secondary analyses will be performed in available cases.

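### For secondary outcomes measured at T1, T2 and T3, available-case tests keep the T1 answers of later non-responders out of the 8-week and 6-month comparisons, mainly at a cost in precision

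*Protocol article*

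**What the plan says.** The Statistical analyses section opens with the primary t test. Its next sentence begins "Secondary interval-scaled outcomes will be tested using". It names two methods, the t test and ANCOVA, and sets one condition for ANCOVA: "if baseline measurement of the outcome is available". Three sentences on analysis sets and missing data close the section:

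- One ties intention to treat to the primary comparison: "The primary analysis will be performed according to the intention-to-treat principle, including all randomized participants".
- One names methods for missing values without saying which analyses they cover: "Missing data will be handled by applying linear mixed models and expectation-maximisation imputation".
- The last sets the remaining analyses apart: "Secondary analyses will be performed in available cases".

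The Secondary outcomes section and Table 1 give the timing:

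- T1, T2 and T3: USE, knowledge, Brief-IPQ, PHQ-9/Core set, acceptance, ZAPA and WHO-5.
- T2 and T3 only: behaviour change, adherence and healthcare utilization.
- T1 only: perceived cultural sensitivity.

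USE is repeated "to investigate the perception of usefulness of the information material over time".

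The Administration section describes collection. At T1, "Patients will read the brochures after the end of the consultation, and will be asked to fill in the questionnaire". At 8 weeks and 6 months, "patients will be contacted by post and asked to fill in follow-up questionnaires". No patient self-rating comes before the brochure is read.

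**The concern.** An available-case test at T2 or T3 uses only the patients who answered at that visit. For the seven outcomes measured three times, the trial will already hold a T1 score on the same scale for many of those who stop responding. That score is correlated with the missing one, and the test ignores it.

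Three things are at stake:

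- Precision. The 8-week and 6-month contrasts are estimated with more variance than the collected data require.
- Bias. If the chance of answering later depends on the T1 score, the responders at T2 and T3 are a selected group. The arm contrast can then shift, provided T1 differs by arm or the selection works differently by arm.
- Readability over time. Each visit is summarised on a different subset, so a description of usefulness over time partly reflects who answered.

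The ANCOVA clause might seem to bring the T1 score back in. It does not, because T1 is itself measured after the intervention.

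**Working it through.** **Inputs from the protocol.** Sample size section: difference 6 points, SD 20 (d = 0.3), Type I error 0.05, power 80%, 280 patients for analysis, about 40% dropout before T1 return, 480 recruited. Statistical analyses section: one-sided test.

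**Inputs not in the protocol (assumptions).** Retention from T1 to T2/T3, correlation between visits, and how strongly dropout depends on T1. Ranges are shown for each.

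**Step 1: the plan's own figure.** n per arm = 2 × (1.645 + 0.842)² × (20/6)² = 2 × 6.185 × 11.11 = 137.4, so 138 per arm and 276 in total, against 280 stated. Inflation: 280/(1 − 0.40) = 467, against 480 stated. Both agree within 3%, and this point does not affect them. Expected T1 responders: 480 × 0.60 = 288.

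**Step 2: how many T1 responses go unused later.** If 10% to 30% of the 288 are lost after T1, that is 29 to 86 patients whose T1 scores do not inform the later comparison.

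**Step 3: precision.** With T1 complete among T1 responders, a proportion π answering later and correlation ρ, the variance of the likelihood-based mean relative to the available-case mean is 1 − ρ²(1 − π).

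| π | ρ | Variance ratio | Equivalent extra patients |
|---|---|---|---|
| 0.90 | 0.5 | 1 − 0.25 × 0.10 = 0.975 | 1/0.975 = 1.03, so 3% |
| 0.70 | 0.6 | 1 − 0.36 × 0.30 = 0.892 | 1/0.892 = 1.12, so 12% |
| 0.60 | 0.7 | 1 − 0.49 × 0.40 = 0.804 | 1/0.804 = 1.24, so 24% |

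In the middle row, 288 × 0.70 leaves about 101 per arm. The standard error of the difference is √(2/101) = 0.141 SD in available cases and 0.141 × √0.892 = 0.133 SD with the T1 information.

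**Step 4: bias.** Simulation with 400,000 patients per arm; correlation 0.5 or 0.7; dropout 25% or 40% of T1 responders; log-odds of dropout falling by 0.5 or 1 per SD of T1 score. In the one-arm settings, the dependence is in the control arm only and overall dropout is equal in both arms.

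| Setting | True later effect (SD) | Available-case difference | Likelihood estimate using all T1 responders |
|---|---|---|---|
| T1 effect 0.30, same dependence in both arms | 0.30 | 0.271 to 0.293 | 0.295 to 0.303 |
| T1 effect 0.30, dependence in one arm only | 0.30 | 0.070 to 0.243 | 0.297 to 0.303 |
| T1 effect 0 or 0.30, dependence in one arm only | 0 | −0.058 to −0.235 | −0.004 to 0.003 |
| T1 effect 0, same dependence in both arms | 0 | −0.005 to 0.004 | −0.003 to 0.003 |

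The first row is a bias of about 0.01 to 0.03 SD, or 0.2 to 0.6 USE points at an SD of 20. The last row shows that selection acting alike in both arms does no harm to the contrast when T1 does not differ by arm.

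**Step 5: ANCOVA on T1.** Adjusting a later score for T1 estimates (later effect) − ρ × (T1 effect). With both effects at 0.30, this is 0.30 − 0.5 × 0.30 = 0.15, or 0.30 − 0.7 × 0.30 = 0.09. The simulation gave 0.146 to 0.153 and 0.086 to 0.094, including the settings where dropout was purely random. The adjustment removes the part of the effect already visible at T1.

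**The case against.** The strongest reply is that the scope is inferred. The missing-data sentence names no analysis, and the available-case sentence speaks of secondary analyses rather than secondary outcomes. The Sample size section also contrasts an intention-to-treat with an available-case analysis of the primary comparison. So the sentence could mean an available-case repeat of the primary analysis, with mixed models intended for the repeated measures. That reading is possible. The order of the sentences favours the other: the missing-data sentence follows the one on the primary analysis, and the available-case sentence then sets the secondary analyses apart. A reader might infer that mixed models are definitely confined to the primary outcome. The text does not go that far, and a clarification would settle it.

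A second reply is that the bias is trivial. This largely stands. With 70% retention, correlation 0.6 and a dropout slope of 0.8 log-odds per SD, a true 0.30 SD comes out at about 0.28. That bias of 0.02 SD is 0.02/0.141, about one-seventh of the standard error from Step 3, and lies towards the null. A reader might infer from the one-arm rows that the planned tests are seriously biased. The protocol gives no reason to expect such dropout: patients and physicians are blinded, the core information is the same in both brochures, and the payment is unconditional. Those rows show what could happen, not what is likely.

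Third, the point does not reach every secondary outcome. Behaviour change, adherence and utilization have no T1 value of their own to lose, and T1 scores are still used in the T1 comparisons. The protocol also plans no within-arm test of change, so changing composition affects the description over time rather than a stated test.

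Fourth, the only dropout that the protocol quantifies is the roughly 40% who do not return the T1 questionnaire. No model of observed outcomes recovers patients who return nothing. This stands and limits the gain.

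**Conclusion.** The point holds for the seven outcomes measured at T1, T2 and T3, on the natural reading of the Statistical analyses section. What can be relied on is a loss of precision: a variance ratio of about 0.89 at 70% retention and correlation 0.6, ranging from 0.975 to 0.804 over the assumptions shown. Bias is a secondary matter. It is about 0.01 to 0.03 SD when T1 differs by 0.30 SD and dropout depends on T1 alike in both arms, and nil when T1 does not differ and the mechanism is the same. It is substantial only under arm-differential dependence, for which the protocol offers no evidence. The ANCOVA option does not repair this. Either its baseline condition is never met and t tests remain, or T1 serves as baseline and a true 0.30 SD shrinks to 0.09 to 0.15 when T1 shows the same effect.

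Retention after T1, the correlation and the dropout slopes are all assumed. The primary analysis and the sample size are untouched. The change is worth making because it uses data already collected and a method the protocol already names.

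**What to change.** For each secondary outcome measured at T1, T2 and T3, replace the per-visit tests with one linear mixed model:

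- Responses: all observed T1, T2 and T3 values. T1 is a response, not a covariate.
- Fixed effects: arm by visit, disease and migration background. Where a symptom scale applies to one disease only, the disease term drops out.
- Physician as a random effect. It is a stratification factor, but has too many levels to enter as fixed effects.
- Unstructured within-patient covariance.
- Report the arm contrast at each visit. For USE, the T1 contrast remains with the primary analysis as planned.

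Keep the available-case tests as sensitivity analysis. Outcomes measured only at T2 and T3 can be modelled jointly over those two visits. Perceived cultural sensitivity, measured once, keeps its available-case test. State explicitly which analyses the missing-data sentence and the available-case sentence cover, and that T1 is not a baseline for ANCOVA.

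The cost is a change of wording and slightly more programming, with no new data. The model relies on data being missing at random given the observed scores, and it does not recover the patients who never return the T1 questionnaire.

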### Sample size

To be able to identify a small intervention effect (Cohen’s *d* of 0.3, which corresponds to a difference of 6 points in the USE (assuming a standard deviation of 20)) with a Type I error of 0.05 and a power of 80%, a total sample size of 280 patients (140 per group) is needed for statistical analysis. Taking into account a dropout rate of about 40% (patients who give informed consent but do not return the questionnaire by post), 480 patients shall be recruited. In the intention-to-treat analysis, the larger number of patients is expected to be compensated by a dilution of effects, meaning that the power will be approximately the same as in the available case analysis.

## Discussion

Our study will provide information on the effects of culturally sensitive patient information material in primary care on central patient-reported outcomes, such as perceived usefulness, disease-related knowledge, behaviour change, perception of disease, illness symptoms, acceptance of disease and treatment, adherence, satisfaction with the physician, health service utilization, and quality of life*.* This will be the first study to use a double-blind, randomized controlled multicentre design to evaluate the effects of culturally sensitive information material. By blinding both patients and the responsible physician, we are likely to control bias caused by expectations. The inclusion of different diseases and migration groups and the recruitment in multiple centres in different areas in Germany should ensure a high external validity of the results.

A central challenge of our study is the complexity of the intervention. The term ‘cultural adaptation’ is not consistently defined in the literature and there are many different ways in which patient information material could be adapted. Therefore, results might be specific to the type of cultural adaptation chosen for our study. However, we aim to describe the process of our cultural adaptation in detail and make it publicly available, to enable a replication and critical discussion of our results. We will take several measures to assure a high quality of the cultural adaptation process and the resulting culturally sensitive patient information material. To ensure a high external validity, only people with a migration background who are living in Germany will be invited to participate in the focus groups. All focus group sessions will be conducted by the same moderators using manuals to ensure high comparability. A high objectivity of our results will be ensured by the use of audio-recording and transcription of the focus group sessions and by the involvement of at least two independent researchers in the analyses of the results.

Potential limitations of the study are that the inclusion criteria (especially the diagnosis) are exclusively based on the clinical judgment of the general practitioners. For feasibility reasons, we chose to include patients regardless of the reason for consultation and we did not specify the timing in the disease course when the patients are eligible. This may dilute the effects of the intervention. Another limitation is that patients have to self-administer a high number of scales. This might hinder the feasibility of the trial and reduce the response rate. Moreover, the use of several self-constructed scales may be critical, as validity and reliability are unknown for some of the scales.

It has often been stressed that cultural adaptation of patient information material is crucial for improving the healthcare of patients with a migration background. However, high-quality studies dealing with this issue are largely lacking. Our study might therefore close an important knowledge gap. The results of our study may have a major impact on health services for patients with a migration background, as they will enable the incremental effect of culturally sensitive patient information material compared with high-quality standard translated material in primary care to be estimated.

## Trial status

The first patient was enrolled in June 2013. At the time of manuscript submission, participants were still being recruited.

## Abbreviations

ANCOVA: Analysis of covariance; Brief-IPQ: Brief Illness Perception Questionnaire; ICD-10: International Classification of Disease, 10th revision; MOS: Medical Outcomes Study; PHQ-9: 9-item version of the Patient Health Questionnaire; SMAS: Stephenson Multigroup Acculturation Scale; USE: Usefulness Scale for Patient Information Material; WHO: World Health Organization; WHO-5: WHO 5 Well-being Index; ZAPA: Questionnaire assessing satisfaction with outpatient care, with focus on patient participation.
